## Abstract

**Background:**

In the Dutch breast cancer screening program, women recalled with a BI-RADS 0 score are referred for additional imaging, while those with BI-RADS 4/5 scores are also directed to an outpatient breast clinic. Approximately six out of ten women are recalled without being diagnosed with a malignancy. However, these recalls require additional imaging and doctor visits, which result in patient anxiety and increased health care costs. Conventional types of imaging used for additional imaging are full-field digital mammography and tomosynthesis. Contrast-enhanced spectral mammography has proved to have higher sensitivity and specificity than conventional imaging in women recalled from screening. Therefore, the aim is to study if CESM instead of conventional imaging is a more accurate, patient-friendly, and cost-effective strategy in the work-up of women recalled from breast cancer screening.

**Methods:**

This prospective, multicenter, randomized controlled trial will be conducted at four centers and will include 528 patients recalled for suspicious breast lesions from the Dutch breast cancer screening program. Participants are randomized in two groups: (1) standard care using conventional breast imaging techniques as initial imaging after recall versus (2) work-up primarily based on CESM. Written informed consent will be collected prior to study inclusion. The primary outcome is the diagnostic accuracy for detection of breast cancer. Secondary outcomes are numbers of additional diagnostic exams, days until final diagnosis, health care costs, and experienced patient anxiety.

**Discussion:**

Based on previously published retrospective studies, we expect to demonstrate in this prospective multicenter randomized controlled trial, that using CESM as a primary work-up tool in women recalled from breast cancer screening is a more accurate, cost-effective, and patient-friendly strategy.

**Trial registration:**

Netherlands Trial Register, NL6413/NTR6589. Registered on 6 July, 2017.

## Background

In the Netherlands, a national breast cancer screening program was introduced in 1990, with full implementation being completed in 1997. All women aged 50–75 years receive an invitation to participate biennially. At mobile screening units, full-field digital mammography (FFDM) is performed. By default, two images are made per breast, one in cranio-caudal (CC) view and one in mediolateral oblique (MLO) view. The images are independently screened for suspicious lesions by two certified screening radiologists. In the case of discrepancy, a third (senior and unblinded) radiologist will make the final decision regarding referral. In the screening recalls, a distinction is made between Breast Imaging Reporting and Data System (BI-RADS) 0 score and BI-RADS 4 or 5 score recalls [1]. Women recalled with a BI-RADS 0 score are directly referred by their general physician (GP) for additional imaging. Women recalled with a BI-RADS 4 or 5 score are first referred by their GP to an outpatient breast clinic, before being directed to a radiology department for additional imaging [2].

Conventional additional imaging may consist of additional (special) FFDM images or digital breast tomosynthesis (DBT), which can be combined with other imaging modalities, such as breast ultrasound (US). Based on the findings during the imaging work-up, tissue sampling might be recommended: either core needle biopsy (CNB), vacuum-assisted biopsy (VAB), or fine-needle aspiration cytology (FNAC). The total work-up in the evaluation of the recalled women can also be extended with breast magnetic resonance imaging (MRI) (e.g., in inconclusive findings) or 6 and/or 12 months follow-up with FFDM, DBT, and/or US.

Approximately six out of ten recalled women from the Dutch breast screening program are not diagnosed with breast cancer [3]. These recalls generate patient distress and anxiety as well as additional doctor visits, medical imaging, and health care costs [3–5]. Also, participation rates for subsequent screening rounds decrease after a recall of women without malignancy [6].

Prior retrospective studies have shown that for these women contrast-enhanced spectral mammography (CESM) proved to be an adequate problem-solving tool, reducing the number of false positives while maintaining high sensitivity [3, 5]. Hypothetically, the use of CESM as an imaging work-up in women recalled from screening reduces the number of additional imaging exams and follow-up doctor visits, potentially saving health care costs [7]. Especially for women with dense breasts, CESM seems to be of additional value, since these women are more at risk of undergoing additional imaging or follow-up after recall due to the low sensitivity of FFDM [8, 9]. Moreover, Houben et al. showed that occult breast cancers are detected when using CESM in up to 4% of women in this population, increasing overall accuracy [10].

Therefore, we propose a prospective, multicenter, randomized controlled trial, aiming to study whether a work-up using CESM instead of conventional imaging modalities such as FFDM or DBT (which is the current standard of care) for women recalled from screening is a more accurate, more patient-friendly, and more cost-effective strategy.

## Methods

The Rapid Access to Contrast-Enhanced spectral mammogRaphy (RACER) study is a multicenter, prospective, randomized controlled clinical trial. Participants will be randomized in two study arms: (1) a control group undergoing standard care, i.e., work-up of recalled women based on conventional imaging (such as FFDM, US, DBT, or MRI) versus (2) work-up primarily based on CESM findings. The follow-up period is 2 years, until the next screening round. Four centers will participate in patient inclusion: the coordinating center Maastricht University Medical Center+ (Maastricht), Zuyderland Medical Center (Sittard-Geleen), Diakonessenhuis (Utrecht), and Laurentius Hospital (Roermond). The study is coordinated (study design, protocol, trial master file, case report forms, and ethical approval) by the research team in Maastricht including the Principal Investigator and Study Coordinator. Each center has a breast radiologist or surgeon as lead investigator and is assisted by other radiologists and technicians in that center for patient inclusion with randomization. Training of new research team members will be done by the Study Coordinator. The Study Coordinator also assists with and is responsible for correct data entry in all centers. Central ethical approval has been confirmed from the Medical Research Ethics Committee of University hospital Maastricht and Maastricht University (decision no. METC171082/NL62788.068.17), and we will not begin recruiting at other centers in the trial until local ethical approval has been obtained.

A data management system with electronic case report forms (eCRFs) is used to manage the clinical data of the participants in anonymous form by their trial identification number. No biological specimens will be collected in this trial. Data entry, access, and storage are restricted to the research teams, and this is monitored. Auditing, including site visits, will be performed by the Clinical Trial Center Maastricht (CTCM) at each center before, during, and at the end of the study. Since this study is marked as a “low-risk study” by the CTCM, a data monitoring committee is not commissioned. Interim analysis and premature termination of the study are not applicable; however, periodic trial progress reports are requested by the main funders of the study. After completion of the study, each center will store all their study data for 15 years.

### Study population

All women recalled for a suspicious breast lesion from our national screening program are eligible for inclusion. Inclusion criteria are the ability to provide written informed consent and being recalled from breast cancer screening during the 18-month study inclusion period. Excluded are women with a known allergy to iodine-based contrast agents and women at risk for developing contrast-induced nephropathy or women with known renal insufficiency, according to the current guidelines.

### Primary and secondary outcomes

The primary outcome will be the accuracy assessed by diagnostic performance parameters, such as sensitivity, specificity, positive predictive value (PPV), negative predictive value (NPV), receiver operating characteristics (ROC) curve, and area under the curve (AUC). Radiologists will prospectively provide a single BI-RADS classification for each exam, where a BI-RADS score of 1–3 will be considered ”benign” and 4-5 ”malignant”. The final BI-RADS score (BI-RADS 1–5), based on imaging, will be compared with the BI-RADS score given by the screening program. The accuracy assessed by diagnostic performance parameters will be assessed after the next screening round after approximately 2 years.

Secondary outcomes will be quality of life (QoL), days until final diagnosis, cost-effectiveness, and experienced patient anxiety during a follow-up of 18 months. Three validated questionnaires will be presented at six different time points (at study inclusion; after 2 and 4 weeks; and after 6, 12, and 18 months). QoL will be assessed by the Dutch version of the EuroQol five-dimension, five-level (EQ-5D-5 L) questionnaire, including a visual analog scale (EQ-VAS). This questionnaire is a preference-based instrument used to value health states [11]. The Dutch tariff for the EQ-5D-5L questionnaire, as established by Versteegh et al., will be used to calculate utility scores per health state [12]. Then the quality-adjusted life years (QALYs) will be modeled based on these utility scores. Resource use related to diagnostics will be collected during the trial.

Health-related anxiety, both state and trait anxiety, will be measured by the Dutch version of the State Trait Anxiety Inventory (STAI-DY-1 and STAI-DY-2) questionnaires. Each STAI has 20 items and will be rated on a 4-point Likert scale, scoring 20–80 points per STAI. A higher score corresponds to a higher anxiety level [13].

For the QoL and STAI scores, inter- and intra-patient differences over time from baseline will be compared including those between the intervention and control group. The scores will also be compared between the women with a follow-up exam after 6 or 12 months and those without this follow-up. Figure 1 shows the outcomes defined by the five outcome elements described by Saldanha et al. [14].

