### Sample size calculation

Prior research showed a specificity of FFDM of 40% in this population [5]. To enable detection of a clinically relevant increase of specificity by 15% (from 40% to 55%), 176 patients without malignant disease per group are required (power 80%, alpha = 5%). The prevalence of malignant lesions in women recalled from the breast screening program is about 30%; thus, 70% have benign lesions. Therefore, a total of 251 women per group (176/0.7) has to be included. To account for 5% loss to follow-up, the final number of patients to be included is 528 (502/0.95). The calculations were done with OpenEpi [20].

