### Statistical analysis

The primary objective of the study is to demonstrate that the use of CESM as a work-up tool for women recalled from breast cancer screening is more accurate compared to standard care consisting of conventional imaging. The secondary objectives are to evaluate whether this novel approach is a more patient-friendly and cost-effective strategy in the work-up of women recalled from breast cancer screening, requiring fewer days until final diagnosis and less additional imaging.

Radiologists will prospectively provide a single BI-RADS classification for each exam, where a BI-RADS score of 1–3 will be considered ”benign” and 4-5 ”malignant”. Based on this cutoff, the final BI-RADS score and recall BI-RADS score, the diagnostic performance parameters sensitivity, specificity, PPV, NPV, and AUC under the ROC curve will be assessed as the primary endpoint for both study arms. Differences in proportions between the two randomized groups will be tested for significance with a chi-square test, and the difference in AUCs will be tested using the method proposed by Hanley et al. [21].

Secondary outcomes are QoL, patient anxiety, and cost-effectiveness. The course of scores on QoL with QALY and patient anxiety (STAI) from baseline over time at the six time points will be visualized and differences between groups will be tested using mixed linear models, which account for correlations between repeated measurements. Single and multiple imputation will be used to replace missing data.

Both intention-to-treat and per protocol analyses will be performed. The per protocol population for the primary outcomes are those who got imaging exams based on their group allocation. Women who underwent CESM in the standard care group are excluded from the per protocol analysis. For the secondary outcomes this population can be further specified to those with questionnaires completed at six time points. *P* values < 0.05 will be considered to indicate statistical significance. Analyses will be performed with SPSS (version 25, IBM Corporation, Armonk, NY, USA) and STATA (version 15, StataCorp LLC, College Station, TX, USA).

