In short, we believe that the prospective multicenter randomized controlled RACER study will show that in recalled women a work-up based on CESM will be more accurate than usual care (based on conventional imaging such as FFDM). Higher specificity at similar sensitivity will reduce false positives and the volumes of additional diagnostic exams required to reach a final diagnosis, ultimately leading to a decrease in health care costs and patient-experienced anxiety during this period.

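### Five accuracy measures share the primary endpoint with no lead measure or success rule, only specificity is powered, and a non-significant test cannot support similar sensitivity

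*Protocol article*

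**What the plan says.** The Primary and secondary outcomes section states: "The primary outcome will be the accuracy assessed by diagnostic performance parameters, such as sensitivity, specificity, positive predictive value (PPV), negative predictive value (NPV", followed by the ROC curve and AUC. Because the list is introduced by way of example, its membership is left open.

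The Statistical analysis section closes the list at five: "the diagnostic performance parameters sensitivity, specificity, PPV, NPV, and AUC under the ROC curve will be assessed as the primary endpoint for both study arms". It then gives the tests. "Differences in proportions between the two randomized groups will be tested for significance with a chi-square test", and AUCs are compared by the Hanley method. One threshold covers everything: P "values < 0.05 will be considered to indicate statistical significance". Intention-to-treat and per protocol analyses are both planned, and neither is given precedence. The objective is to demonstrate that CESM "is more accurate compared to standard care consisting of conventional imaging".

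The Sample size calculation section uses one measure only: "To enable detection of a clinically relevant increase of specificity by 15" percentage points, from 40% to 55%. No sensitivity is given for either arm, and no margin or power for it.

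The Discussion closes with the expected result: "Higher specificity at similar sensitivity will reduce false positives".

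**The concern.** The endpoint has five components, the sample size has one, and nothing connects them to the claim. Specificity could rise while sensitivity falls, or PPV alone could reach significance. In either case the plan does not say whether the primary objective is met. That choice would be made after the results are known, and an error rate above the nominal level follows if any favourable measure is accepted.

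Sensitivity raises a separate problem. The expected result pairs a gain in specificity with no loss of sensitivity, yet the only planned comparison of sensitivity is a test for a difference. Failing to find a difference in a small number of cancers does not show that there is none. This matters because the section on the reference standard lets a negative CESM rule out malignancy and expects follow-up exams to be omitted.

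**Working it through.** **1. The plan's own figure.** Inputs from the Sample size calculation section: p1 = 0.40, p2 = 0.55, alpha 5% (taken as two-sided), power 80%. With mean proportion 0.475:

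n = [1.96·√(2·0.475·0.525) + 0.8416·√(0.40·0.60 + 0.55·0.45)]² / 0.15² = (1.384 + 0.588)² / 0.0225 = 172.8, so 173.

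The stated 176 is within 2% of this and gives 80.7% power. Then 176/0.7 = 251 per group and 502/0.95 = 528. The calculation reproduces, for specificity as a single two-sided 5% test.

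**2. Error rate if any one of the five measures sufficed.** The bound for five independent tests is 1 − 0.95⁵ = 22.6% in either direction, and 1 − 0.975⁵ = 11.9% in favour of CESM. The measures are correlated, so the rate was simulated:

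- 200,000 null trials per scenario, 251 per arm, 30% prevalence (both from the protocol).
- Equal accuracy in both arms: specificity 0.40 or 0.55 (the protocol's figures), sensitivity 0.85–0.97 (assumed).
- Chi-square tests on the four proportions and a z-test on AUC, with several AUC variances tried.

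| Event under no true difference | Simulated | Nominal, single test |
|---|---|---|
| At least one of five significant, either direction | 14.9–18.0% | 5% |
| At least one of five significant in favour of CESM | 7.5–9.1% | 2.5% |

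A second simulation gave about 14–17% and 7–9%, so the ranges quoted are 14–18% and 7–9%.

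**3. What the trial can say about sensitivity.** Cancers per arm: 251 × 0.30 = 75.3, about 75. The 95% CI half-width for the difference is 1.96·√(2·s(1 − s)/75), where s is the common sensitivity:

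| Assumed s | Half-width (points) |
|---|---|
| 0.97 | 5.5 |
| 0.95 | 7.0 |
| 0.90 | 9.6 |
| 0.85 | 11.4 |

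Power of the chi-square test at 75 per arm, by exact enumeration from an assumed 95%:

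- fall to 90%: 22% (normal approximation 21%)
- fall to 85%: 55% (normal approximation 53%)
- fall to 80%: 83%

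A five-point loss would therefore be missed about four times in five, and a ten-point loss nearly half the time.

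**4. Cost of the alternatives.** Specificity as the sole primary test keeps 80.7% power at 176 per group. Bonferroni over five tests (alpha 0.01) would need 258 women without malignancy per group. At 176 it would leave about 60% power.

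**The case against.** The best defence is that specificity already leads in practice, since the sample size is built on it, and that a condensed article may leave testing order and interval methods to an analysis plan. The first part is fair and is why the repair is cheap. The second does not remove the point, because the article itself fixes the five-part primary endpoint, the tests and the threshold. Naming one measure would change what is published, not add detail to it.

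Four stronger readings are tempting, and the documents do not support them.

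- *A reader might infer a 16–18% chance of wrongly declaring CESM more accurate.* A rate of that size counts differences in either direction, including those against CESM. The objective is directional, and the matching figure is about 7–9%.
- *A reader might infer that success could rest on any one of ten P values.* The protocol states no such rule. The ten would count two heavily overlapping analysis sets as separate chances, and the simulation covers five tests. Even the five-test figures depend on an any-one-suffices reading.
- *A reader might infer that the chi-square test is unreliable for sensitivity because few false negatives are expected.* At 95% sensitivity the expected count is 75 × 0.05 = 3.75 per arm, but the exact size of the test there is 4.9%. At 90% it is 5.1%, and at 97% it is 4.3%. The 95% is itself an assumption; at 90% the expected count is 7.5.
- *A reader might infer that the analysis is blind to a loss of sensitivity.* Sensitivity is a named measure with a between-arm test, and a fall from 95% to 80% would be detected with 83% power. The weakness lies with modest losses.

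It is also true that similar sensitivity is an expectation in the Discussion, not a stated equivalence objective. The fault is that the planned test could not support it, not that a planned equivalence test was done wrongly.

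**Conclusion.** The point holds. The primary endpoint is badly fixed: five measures, no lead measure, no success rule, no order between the two analysis sets, and a sample size for one measure only.

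The size of the error inflation is conditional. It rests on treating any one significant measure as success, on 30% prevalence with 251 per arm, and on an assumed common sensitivity of 0.85–0.97. Under those conditions it is about 14–18% for any false difference and about 7–9% for a false claim favouring CESM, against nominal rates of 5% and 2.5%.

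The sensitivity point does not depend on multiplicity. With about 75 cancers per arm, the difference is known only to within about 5–11 points over the same assumed range. P > 0.05 would be weak evidence of similarity.

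**What to change.** - Name specificity at the stated BI-RADS cut-off, in the intention-to-treat population, as the single primary endpoint, tested at two-sided 5%. This matches the Sample size calculation section and leaves both the sample size and the 80% power unchanged.
- Make sensitivity the key secondary endpoint. Report the between-arm difference with a 95% CI, read against a margin that the investigators state in advance, and make no claim of similarity from P > 0.05.
- Report PPV, NPV and AUC with confidence intervals as supportive measures.
- Treat the per protocol analysis as a sensitivity analysis.

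The cost is a wording change in the two sections that define the primary endpoint. There are two consequences. A significant PPV, NPV or AUC alone can no longer carry the primary claim. And the trial may be too small for a narrow sensitivity margin. Using n = (1.96 + 0.8416)²·2·0.95·0.05/margin², with 95% sensitivity assumed in both arms and 80% power, a 10-point margin needs 75 cancers per arm and a 5-point margin needs 299. These margins only illustrate what about 75 cancers per arm can show; neither is a recommendation.

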### The control group: usual care with conventional breast imaging

Women undergoing standard of care will have their screening FFDM re-evaluated, adding (special) FFDM views, DBT, or US if deemed necessary. In FFDM and DBT, the breast is compressed between a paddle and detector plate. The laterality of the breast and views per breast depend on the judgment of the radiologist. At least one additional view of the recalled side will be performed. Tissue sampling (CNB, VAB, FNAC) can be recommended to support or to invalidate suspicious findings on imaging. In case of inconclusive findings, the radiologist can consider follow-up in 6 and/or 12 months or single breast MRI. The use of CESM is not permitted in this study arm.

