### Establishment of final diagnosis (the reference standard)

For the control group, final diagnoses of the (recalled) breast lesions can be divided into four categories [3, 5]: (1) simple cysts; (2) superposition densities; (3) solid, benign masses; (4) (invasive) breast cancer or ductal carcinoma in situ (DCIS). The first three groups are defined as benign findings. To ascertain a final diagnosis of (1), targeted US is performed, followed by cyst aspiration and a second FFDM of that breast to confirm that the lesion has disappeared. Final diagnosis of (2) requires a minimum of one special view or DBT, including targeted US. To rule out false negative (FN) findings, 6 and/or 12 months follow-up or breast MRI can be considered. Final diagnosis for categories (3) and (4) is acquired with US-guided or stereotactic tissue sampling. If cancer or DCIS is diagnosed, the subject will have a ”true positive” (TP) finding. In subjects where no breast cancer or DCIS is diagnosed, the follow-up period of 2 years will determine the true disease status. If no interval cancers have been detected and the subject has not been recalled in the subsequent screening round, the case will be considered a ”true negative” (TN).

In the CESM group, diagnoses are acquired slightly differently. For (1), CESM will show an ”eclipse sign” which is pathognomonic for cysts [3]. No further action is needed. For category (2), a negative CESM exam with no suspect lesion on both low-energy and recombined images rules out (pre)malignant lesions due to CESM’s high negative predictive value [3, 5]. To acquire final diagnoses of (3) and (4), CESM and targeted US are performed including tissue sampling for pathological confirmation.

Since most benign recalls are caused by cysts or superposition densities, the investigated intervention will most likely result in fewer additional exams and tissue samplings among these recalls [3, 5]. Moreover, follow-up exams can be omitted, which is more patient-friendly, and hypothetically, more women will attend the subsequent screening round when they are examined with CESM.

A flow chart is presented in Fig. 3, summarizing the study design, the randomization process, and the establishment of the different diagnoses.

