Using CESM as a work-up tool also has some limitations. The most important disadvantages are the increased radiation dose and the administration of iodine-based contrast agents. Regarding the increase in radiation dose, several studies have shown that the mean radiation dose of CESM per exposure is in the range of 2.5-2.8 mGy [18, 31–33]. In comparison, the radiation dose of FFDM in these studies varied from 1.4 to 1.8 mGy. Jeukens et al. showed that the CESM radiation dose is approximately 80% higher than that in FFDM: 2.8 mGy versus 1.6 mGy, respectively [18]. Nevertheless, it is still within internationally accepted limits and does not substantially increase breast cancer incidence or mortality in women recalled from screening, who are at least 50 years. We believe that this increased dose is justified in the dedicated population as outlined. The chance of acquiring breast cancer due to this radiation exposure is expressed in the life attributable risk (LAR) numbers. For example, for a single view CESM acquisition having a mean radiation dose of 2.8 mGy per exposure, the LAR number for cancer incidence is 0.4 in 100,000 persons at the age of 60 years [34]. The LAR number for cancer mortality at this age is even 2–3 times lower. Some even advocate that there is no effect of radiation under a dose of 100 mSv. Hence, one may conclude that CESM exposure poses only a small additional risk compared to the lifetime risk for breast cancer incidence and mortality of 12,000 and 3000 cases per 100,000 women, respectively.

Regarding the use of iodine-based contrast, Houben et al. had in clinical practice in a similar population a low incidence (0.6%) of adverse hypersensitivity reactions [10]. In contrast, they also showed that occult cancers are being detected in 3–4% of the recalled women by using CESM. Consequently, the chance of finding occult (small) breast cancers is higher than the chance of having adverse reactions to contrast administrations (which are all documented in the RACER study), which in our opinion would justify the use of a CESM-based work-up of women recalled from screening.

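### The accuracy rule does not match the BI-RADS 4–5 call to the site of the cancer, which probably overstates control-arm sensitivity

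*Protocol article*

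**What the plan says.** **Index test.** In the protocol article, under Primary and secondary outcomes and again under Statistical analysis, "Radiologists will prospectively provide a single BI-RADS classification for each exam", with 1–3 taken as benign and 4–5 as malignant. Statistical analysis continues: "Based on this cutoff, the final BI-RADS score and recall BI-RADS score, the diagnostic performance parameters sensitivity, specificity, PPV, NPV, and AUC" are the primary endpoint in both arms.

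**Reference standard.** The section on establishing the final diagnosis works at the level of the subject. "If cancer or DCIS is diagnosed, the subject will have a" true-positive finding. Otherwise, "In subjects where no breast cancer or DCIS is diagnosed, the follow-up period of 2 years will determine the true disease status". The condition for a true negative also names no breast: "If no interval cancers have been detected and the subject has not been recalled in the subsequent screening round". The section lists four diagnosis categories for recalled lesions, but does not link a category to the BI-RADS score or to the site of a later cancer.

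**Coverage.** CESM takes two views of each breast. In the control arm the screening mammogram is re-evaluated and at least one extra view of the recalled side is made. Beyond that, "The laterality of the breast and views per breast depend on the judgment of the radiologist".

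**Cancers away from the recalled lesion.** The Discussion expects them. Of an earlier cohort in a similar population it says "they also showed that occult cancers are being detected in 3–4% of the recalled women by using CESM".

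**The concern.** Neither axis of the two-by-two table carries a location. Take a woman whose recalled lesion is called BI-RADS 4 and proves benign, and who has a cancer elsewhere that the work-up did not flag. If that cancer surfaces within 2 years, the cutoff makes her test-positive and the follow-up makes her diseased. She is counted as a detected cancer, although the call was a false alarm and the cancer was missed.

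The credit grows with an arm's false-positive rate and with the number of cancers that it misses away from the recalled lesion. The plan expects the control arm to be higher on the first, and its case for CESM implies the same for the second. Sensitivity is a named primary parameter, and the Discussion anticipates higher specificity at similar sensitivity. A rule that turns missed cancers into detected ones, mainly in one arm, makes the two sensitivities look more alike than they are. PPV and AUC are affected in the same way.

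**Working it through.** **The plan's own figure.** For 40% versus 55%, power 80% and alpha 5% (two-sided assumed), the pooled formula gives (1.96 + 0.8416)² × 2 × 0.475 × 0.525 / 0.15² = 174 per group. The version with separate null and alternative variances gives 173. The stated 176 agrees closely. Then 176/0.7 = 251 per group and 502/0.95 = 528. These counts concern women without malignancy. The women at issue here have cancer under either scoring, so they do not enter specificity.

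**Inputs from the document.** 251 women per arm; 30% prevalence; false-positive rate f = 1 − 0.40 = 0.60 in control and 1 − 0.55 = 0.45 for CESM (Sample size calculation); occult cancers in 3–4% of women, as detected by CESM (Discussion).

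**Assumptions not in the document.** 95% sensitivity at the recalled lesion; the occult share that control misses; the share of these in women whose recalled lesion is benign (70%, taken from the benign proportion); the share s surfacing within 2 years; the call on the benign lesion independent of the occult cancer.

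**Formulas.** Cancers at the recalled lesion: 0.30 × 251 = 75.3, of which 0.95 × 75.3 = 71.5 are detected. Let M be the women with a benign recalled lesion and a missed cancer elsewhere that surfaces.

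- Matched sensitivity = 71.5 / (75.3 + M)
- Unmatched sensitivity = (71.5 + f·M) / (75.3 + M)
- Overstatement = f·M / (75.3 + M); the assumed 95% drops out

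**Control arm, f = 0.60**

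| Occult share × share without index cancer | s | M | f·M | Matched | Unmatched | Overstatement |
|---|---|---|---|---|---|---|
| 3% × 70% | 0.25 | 1.3 | 0.8 | 93.4% | 94.4% | 1.0 |
| 3% × 70% | 0.50 | 2.6 | 1.6 | 91.8% | 93.8% | 2.0 |
| 3% × 70% | 1.00 | 5.3 | 3.2 | 88.8% | 92.7% | 3.9 |
| 4% × 100% (upper bound) | 1.00 | 10.0 | 6.0 | 83.8% | 90.9% | 7.1 |

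If the control false-positive rate were 30% (an assumption), every overstatement would halve; the first three rows become 0.5, 1.0 and 2.0 points.

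**CESM arm.** With the same M = 5.3, f = 0.45 gives 0.45 × 5.27 / 80.57 = 2.9 points. With f = 0.123 (1 − the 87.7% specificity that the Discussion cites from a retrospective study) it is 0.8 points. M itself should be smaller if CESM finds these cancers at work-up. Both effects point to a larger overstatement in control.

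**Against random error.** At 95% sensitivity in 75.3 cancers, the 95% half-width is 1.96 × √(0.95 × 0.05 / 75.3) = 4.9 points per arm, and 4.9 × √2 = 7.0 points for the difference.

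**The case against.** The strongest reply is that the article nowhere labels such a woman a true positive. Its reference-standard section attaches that label to a diagnosed cancer, most naturally one found at work-up, and then says only that follow-up decides the rest. This is correct as far as it goes. A reader might infer that the text itself calls the false alarm a detection; it does not. The result follows from applying the stated cutoff to the stated 2-year status, which is what the analysis section needs in order to compute sensitivity.

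A second reply is that matching by side or quadrant is coding detail for the full protocol, the case report forms or an analysis plan. That would hold if the article were silent on the unit. It fixes one score per exam, twice, and a subject-level status. The reference to recalled lesions only lists diagnosis categories.

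Third, one might infer that the control work-up looks only at the recalled side. It does not: it starts from re-evaluating the screening mammogram, which the Background describes as two views of each breast, and ultrasound, tomosynthesis or MRI may be added. The difference between arms lies in guaranteed new imaging of both breasts.

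Fourth, the inputs lean high. The 60% is one minus a mammography-only specificity, while the scored value is the final BI-RADS in an arm that may use more modalities. The 3–4% is what CESM detected, not what control misses. Both points stand and limit the size.

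Finally, the bias probably favours control, so it is conservative for a superiority claim. That also stands, but it does not help a reader who wants a fair estimate of sensitivity in each arm.

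**Conclusion.** The point holds as a cheap improvement to the endpoint definition. As written, the rule places a 4–5 call on a benign lesion plus a later cancer elsewhere in the true-positive cell, and this probably overstates control sensitivity more than CESM sensitivity.

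The plausible size is about 1 to 4 points under the assumptions above, or roughly one to three women among about 75 to 80 cancers, and less if the control false-positive rate is below 60%. A reader might take about 7 points as the expected bias. The document does not support that. It would need every occult cancer to be missed in control, to lie in a woman with a benign recalled lesion, and to surface within 2 years; it is an upper bound.

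Nor does the point undermine the powered comparison. Specificity and the total of 528 are essentially unaffected, and the plausible bias is smaller than the random error of the sensitivity difference.

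**What to change.** Keep the woman as the unit and add one rule to the endpoint definition, applied identically in both arms:

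- From existing radiology and pathology reports, code side and lesion location (quadrant) for the finding behind each BI-RADS 4–5 score and for each proven cancer.
- Count a true positive only when the two match. A cancer away from the recalled lesion that the index work-up itself flagged as 4–5 remains a true positive.
- Count a woman with a 4–5 call only on a benign lesion and an unflagged cancer elsewhere as a false negative.
- Where only the side can be established, match on side and flag the case, because a missed cancer elsewhere in the same breast may still be credited.
- Report the unmatched woman-level result as a sensitivity analysis.

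The cost is some coding work and a few ambiguous locations to settle. Accuracy is assessed only after the next screening round, so the rule can be set before analysis. The sample size does not change.
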